### Measurements

The time-points of the follow-up measurements are tied to the estimated stop-date, which is appropriate for aid-to-cessation trials [26]. The expected stop-date is 3 months after treatment start, which is later than in common cessation treatments where quitting usually is expected within 1 to 3 weeks. In total there will be four follow-up measurements with measurement 3 and 4 (9 and 15 months follow-up) to be conducted at standard time points (i.e. 6 and 12 months after the expected stop-date):3 months after treatment start, expected stop-date, (3 months follow-up);6 months after treatment start, end of treatment and 3 months after expected stop-date, (6 months follow-up);9 months after treatment start, 3 months after end of treatment, 6 months after expected stop-date, (9 months follow-up); and15 months after treatment start, 9 months after end of treatment, 12 months after expected stop-date, (15 months follow-up).

A measurement schedule can be found in Table 2. The biochemical measurements will be done when the patient is at the hospital for a face-to-face session in week 1 (Exhaled CO; baseline/month 0), week 14 (Exhaled CO & Cotinine level; month 3) and week 22 (Exhaled CO; month 5). For the final biochemical measurement (Exhaled CO & Cotinine Level; month 15) which will take place 12 month after the expected stop date in month 3, the patient will have to return to the hospital. All other assessments will be done using online questionnaires which the patients will complete at home.

**Table 2 Tab2:** Measurement schedule

Variables	Measurement at month					
	0	3	5	6	9	15
Primary outcome						
Cotinine level		X				X
Secondary outcomes						
Nicotine dependence (Fagerström)	X			X	X	
MAP-HSS + smoking related complaints of smokers	X			X	X	X
Depression, anxiety and stress (DASS21)	X			X	X	X
Quality of Life (Euroqol 5D)	X			X		
Smoking status	X	X		X	X	X
Adherence						X
Costs						X
Baseline predictors and moderators of treatment effect						
Internet Skills	X					
Readiness to change	X					
Attitude	X			X	X	
Social Influence	X					
Self-Efficacy	X			X		
Alcohol/substance (mis)use	X			X		
Descriptive variables						
Patient characteristics and medical history	X					
Smoking history	X					
Stop Smoking History	X					
Other information of interest						
Evaluation of treatment		X		X	X	X
Exhaled carbon monoxide (CO) level	X	X	X			X

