The CO measurements in the study will serve as a backup for the cotinine measurements. They will only be analyzed in case the saliva samples are not usable. This backup strategy has been chosen because CO measurements are part of the routine stop-smoking treatment. To keep the burden for the participating patients as low as possible the measurements are linked to the scheduled face-to-face sessions. As the last face-to-face session in both treatment groups usually takes place in week 22 this moment has been chosen for the measurement to prevent the patient from travel time/work time loss for an extra appointment because of the study.

During the informed consent procedure all participants will receive a patient information letter that outlines the burden of participation, including the online questionnaires. By stressing the importance of the online questionnaires we try to increase patient commitment. During the trial, completion of the questionnaires will be checked after 2 weeks. Participants not completing the questionnaire will receive four weekly reminders: first twice via email, then twice by telephone. If a participant signals to be struggling with completing the questionnaire online, we will offer a paper version of the questionnaire, which will be sent including a return envelope.

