## Instruments

### Primary outcome (Cotinine level)

The primary outcome parameter will be biochemically validated prolonged abstinence [26] at 15 months from the start of the smoking cessation treatment. Saliva cotinine level will be measured as biochemical verification of abstinence only by those patients that report quitting smoking in the previous online questionnaires [27]. Prolonged abstinence is defined as having salivary cotinine levels < 20 ng/ml [28] that validate both the self- reported abstinence after the self-chosen stop date – usually 3 months after start - and the self-reported abstinence at 15 month follow-up. Patients not reporting abstinence or with a higher cotinine level on any of these follow-ups will be regarded as smokers as well as patients who are lost to follow-up. A 0,5–1 ml salivary sample will be collected for cotinine assessment by means of a Salivette (Sarstedt AG & Co., Nümbrecht, Germany). Under supervision, patients will have to chew on a cotton swab for 1min to stimulate the saliva flow rate. All saliva specimens will be frozen until assayed and transported to the laboratory for the determination of the cotinine level using a gas chromatography technique.

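### The first abstinence check follows a self-chosen stop date in the definition but a fixed week-14 visit and a prior questionnaire in the schedule, so some genuine quitters can be counted as smokers

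*Protocol article*

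**What the plan says.** Protocol article, Primary outcome (Cotinine level): prolonged abstinence needs a salivary cotinine below 20 ng/ml confirming self-report at two points. The first is "abstinence after the self-chosen stop date – usually 3 months after start"; the second is month 15. Saliva is taken "only by those patients that report quitting smoking in the previous online questionnaires". The failure rule is "Patients not reporting abstinence or with a higher cotinine level on any of these follow-ups will be regarded as smokers", and patients lost to follow-up are also classed as smokers.

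Protocol article, Measurements: "The expected stop-date is 3 months after treatment start". The first follow-up questionnaire is placed at "3 months after treatment start, expected stop-date, (3 months follow-up". The first cotinine sample is at "week 14 (Exhaled CO & Cotinine level; month 3"; Table 2 shows the next at month 15 and none between. For late forms, "completion of the questionnaires will be checked after 2 weeks" and "Participants not completing the questionnaire will receive four weekly reminders".

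The CO backup appears twice. Under Measurements, CO is analysed only when saliva samples cannot be used. Under Exhaled carbon monoxide (CO) level, it is used when cotinine measurements are missing. Table 2 lists CO at months 0, 3, 5 and 15.

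**The concern.** The definition follows the patient's own stop date and the schedule follows the calendar. The word *usually* admits stop dates other than month 3, and the Study intervention section lets patients set their own quit date or step down until they are ready. No window or grace period is stated for the first validation, and no later first sample is provided.

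The sample also depends on a form due on the day the patient is expected to stop, and the procedure for chasing that form begins after the sampling visit. Primary success would then depend partly on when a form was completed.

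This matters more in a non-inferiority trial with an absolute margin. If the same fraction of quitters is lost in both arms, both rates shrink and so does the difference between them, while the 5-point margin stays put. That favours a non-inferiority conclusion.

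**Working it through.** **1. The plan's own sample size.** Inputs (Sample size section): TAU 10%, BSCT 15%, margin 5 points, α 0.025, power 80%.

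n per arm = (1.960 + 0.842)² × (0.10×0.90 + 0.15×0.85) / (0.05 + 0.05)² = 7.849 × 0.2175 / 0.01 = 170.7, so 171 against 172 stated. The figure is reproduced.

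**2. The calendar.**
- Three months = 365.25/4 = 91.3 days = week 13.0. This is both the expected stop date and the due date of the month-3 questionnaire.
- Week 14 = days 92 to 98. A patient who stops on schedule has about 0 to 7 days of abstinence at the sample.
- Completion check: 13 + 2 = about week 15.
- Fourth weekly reminder: week 18 if the first goes out at the check, week 19 if a week later.
- The check and reminders therefore fall about 1 to 5 weeks after the only early cotinine visit.
- Before week 14, Table 2 lists smoking status only at months 0 and 3, so the month-3 form is in effect the gate.

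**3. Who is affected under the rules as written.**

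| Patient | Outcome |
|---|---|
| Stops by month 3, answers after stopping and before the visit | Sampled; can succeed |
| Answers just before stopping | Reports smoking, no sample, can be classed as smoker |
| Stops a few days after the form or visit | Same |
| Abstinent, answers after the visit | No cotinine; CO counts under one wording and not under the other, so undetermined |

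**4. Size, under an assumed loss.** The documents give no share of quitters lost, so f is an assumption. Multiply both rates by (1 − f), with 172 per arm, and claim non-inferiority if the lower limit of the 95% Wald interval for BSCT minus TAU exceeds −5 points. Probabilities are summed exactly over all pairs of binomial counts.

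| f, both arms | True 10% v 5% observed as | False non-inferiority | Power, true 10% v 15% |
|---|---|---|---|
| 0 | 10% v 5% | 3.1% | 81% |
| 10% | 9% v 4.5% | 4.7% | 81% |
| 30% | 7% v 3.5% | 10.9% | 81% |

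The normal approximation shows the same pattern: 2.5%, 3.8% and 9.1%. For example, at f = 30%, SE = √[(0.07×0.93 + 0.035×0.965)/172] = 0.0240, and Φ[(0.05 − 0.035)/0.0240 − 1.96] = Φ(−1.33) = 9.1%. The 3.1% at f = 0 exceeds 2.5% because of the Wald interval and not because of any loss. The increase due to loss is 4.7 − 3.1 = 1.6 points to 10.9 − 3.1 = 7.8 points.

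**The case against.** A reader might infer that everyone who quits on schedule, and every late responder, is counted as a smoker. The documents do not support that. An on-schedule quitter who answers between stopping and the visit is sampled. A late responder who reports abstinence fits none of the failure categories, and the wider CO wording would use the week-14 reading.

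Month 3 may itself act as a grace period. The article notes that quitting is usually expected within 1 to 3 weeks elsewhere, and the Readiness to change section classifies planned stop moments as within 1 month or within 2 or 3 months. This suggests the number stopping after month 3 may be small. It does not remove the conflict, since the definition still names the self-chosen date.

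Losing patients who stop well after week 14 is largely inherent in a 12-month outcome read at month 15. That stands, and it is why late quitters should not simply be moved into the primary endpoint.

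The loss shares are assumed. The 10% planning rate is already a cotinine-validated intention-to-treat rate, so shrinking it further may double-count. That also stands, and the table is therefore an illustration. A reader might also infer that loss differs between arms because online sessions change the pace of quitting. Nothing in the documents shows this, and minimization on quitting strategy limits imbalance in gradual quitters.

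Finally, how a self-report triggers sampling could be detail held in the full protocol. But the article does state the gate, the fixed visit, the check interval and both CO rules, and those are what conflict.

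**Conclusion.** The point holds in limited form. Followed as written, the plan can lose genuine quitters from the primary endpoint: those who answer the month-3 form just before stopping and those who stop a few days late. Abstinent late responders have no determined status until the two CO rules are reconciled.

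How many patients this affects cannot be read from the documents. Under an assumed equal loss of 10% to 30% in both arms, false non-inferiority at true rates of 10% v 5% rises from 3.1% to between 4.7% and 10.9%, with power at the planned rates essentially unchanged. These figures rest on the assumed shares, equal loss in both arms, 172 per arm, a Wald interval, and 10% and 5% being the rates before any such loss. The case for the change does not depend on them, because the definition and the schedule disagree whatever the share.

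**What to change.** - **Sampling.** At the week-14 visit, collect and freeze saliva from every patient who says at that visit that they have stopped. Assay it once the questionnaire, including a late one, confirms abstinence. The visit is face-to-face in both arms and specimens are already frozen until assay.
- **Definition.** Reconcile the Primary outcome section with the Measurements section by stating which stop dates, and what window or grace period, count for the first validation.
- **CO backup.** Align the two wordings so that week-14 CO is used when cotinine is missing.
- **Primary outcome and sensitivity analysis.** Keep 12-month prolonged abstinence at month 15 as primary. Report validation of later quitters at week 22 (CO plus the 6-month self-report) only as a sensitivity analysis. Month 15 is about week 65, so week 22 leaves 65 − 22 = 43 weeks, roughly 10 months, and including these patients in the primary analysis would change the endpoint.

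The cost is some extra swabs at an existing visit and a few sentences of endpoint wording.

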### Study intervention

BSCT will be a combination of face-to-face treatment combined with web-based treatment into one integrated smoking cessation treatment that can be delivered in conventional smoking cessation clinics [12, 14]. Both BSCT and TAU will be provided by the Outpatient Smoking Cessation Clinic (SRP), which is part of the Department of Pulmonary Medicine of MST hospital. The web-based interaction of BSCT – which patients will do e.g. at home - will make use of Tactus Addiction Treatment’s website http://www.rokendebaas.nl. Out of this web-based treatment five session have been adopted for the integration in BSCT (Table 1). The SRP team consists of a pulmonologist and three qualified stop-smoking counsellors. The counsellors are registered on the Dutch Quality Register of qualified smoking cessation counsellors (http://www.kwaliteitsregisterstopmetroken.nl). Both treatments fulfil the requirements of the Dutch care module for smoking cessation [19] which is derived from the evidence-based Dutch Guideline Treatment Tobacco Addiction [20]. The costs of smoking cessation treatment will be reimbursed by the patient’s health care insurance.

**Table 1 Tab1:** Distribution of the behaviour change techniques in the face-to-face and online session in BSCT and TAU

Session/week	Name (Code) of the main behavioural change techniques according to [20]	TAU	BSCT
Session 1, week 1 Goal setting	Provide information on consequences of smoking and smoking cessation (BM1) Provide rewards contingent on successfully stopping smoking (BM4) Identify reasons for wanting and not wanting to stop smoking (BM9) Facilitate goal setting (BS4) Prompt self-recording (BS6) Advise on stop-smoking medication (A1) Advise on/facilitate use of social support (A2) Build general rapport (RC1) Explain expectations regarding treatment programme (RC4)	Face-to-face	Face-to-face
Session 2, week 3 Measures for self-control	Provide feedback on current behaviour (BM3) Provide rewards contingent on effort or progress (BM7) Facilitate barrier identification and problem solving (BS1) Facilitate relapse prevention and coping (BS2) Prompt review of goals (BS5) Prompt self-recording (BS6) Advise on changing routine (BS7) Tailor interactions appropriately (RD1)	Face-to-face	Online

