### Other information of interest

#### Evaluation of treatment

Three month after start of the treatment, at the end of the treatment (6 month after start) and during the follow-up measurements (9 and 15 month after start) patients will be asked to report their experiences with the different aspects of the treatment program. Patients can rate satisfaction with the program by grading all separate types of contact, assessing the overall contact with their counsellors, and reporting their own perception of improvements. In addition, they will be asked to report on adherence, results and benefits, gained insights, the use of co- interventions, and the use of NRT. Furthermore, they will be asked for improvement suggestions.

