#### Exhaled carbon monoxide (CO) level

The measurement of exhaled carbon monoxide (CO) level provides an immediate, non-invasive method of assessing smoking status [45]. A breath CO level of 5 ppm is taken as the cut-off between smokers and non-smokers (5 ppm or higher = smoker, less than 5 ppm = non-smoker). Breath CO monitoring will be performed using a piCo Smokerlyzer (Bedfont Instruments: Kent, UK), a portable CO monitor.

The level of exhaled carbon monoxide (CO) level will be recorded because the CO measurement is already part of the treatment so that these data is easily available. Because the validation of the smoking cessation is done with cotinine tests (see above) the CO data will only be used if cotinine measurements are missing and to provide data for future research such as for example comparing different measurement techniques.

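### The cotinine rule can class abstinent NRT users as smokers, and the plan does not let the same-visit CO reading correct it; the size of the effect is unknown

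*Protocol article*

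**What the plan says.** **Endpoint rule.** Protocol article, Primary outcome (Cotinine level): "Prolonged abstinence is defined as having salivary cotinine levels < 20 ng/ml". This must hold both after the self-chosen stop date, usually month 3, and at month 15. The section then states: "Patients not reporting abstinence or with a higher cotinine level on any of these follow-ups will be regarded as smokers". NRT is not mentioned, so one value of 20 ng/ml or more at either check is decisive.

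**NRT is foreseen.** Table 1 (Study intervention) lists, for session 1, "Advise on stop-smoking medication (A1". That session is face-to-face in both arms. Under Evaluation of treatment, patients report "the use of co- interventions, and the use of NRT" at months 3, 6, 9 and 15. The Smoking status section counts e-cigarettes as tobacco consumption but does not list NRT.

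**CO is measured but restricted.** Measurements and Table 2 place CO and cotinine together at week 14 (month 3) and at month 15. On the CO readings, Measurements says: "They will only be analyzed in case the saliva samples are not usable". The CO section says: "the CO data will only be used if cotinine measurements are missing", and adds a future-research purpose. It sets 5 ppm as the cut-off between smokers and non-smokers.

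**The concern.** Cotinine is a metabolite of nicotine whatever its source, and NRT produces no carbon monoxide. This is general pharmacology and the only fact here that the protocol does not state. A patient who has stopped smoking and uses NRT can therefore have a technically valid cotinine result above the cut-off. Such a sample is neither missing nor unusable, so both CO clauses exclude the reading that could settle the matter. The week 14 sample also falls inside the 26-week treatment period, when NRT use is plausible.

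Two consequences follow for the non-inferiority comparison. If the loss of true quitters is proportionally equal in the arms, both rates shrink, and the absolute difference shrinks with them while the margin stays at 5 points. A truly inferior treatment then passes more easily. If NRT use differs between arms, the difference itself is biased, in either direction.

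**Working it through.** **Inputs from the protocol** (Sample size; Data analysis/Statistical methods): TAU 10%, BSCT 15%, margin 5 points, α 0.025, power 80%, 172 per group, decision by the 95% confidence interval of the difference.

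**Reproducing the plan's figure.** With unpooled variance, n = (1.960 + 0.842)² × [0.10 × 0.90 + 0.15 × 0.85] / (0.15 − 0.10 + 0.05)² = 7.849 × 0.2175 / 0.01 = 170.7, so 171 per group against 172 stated. Power at 172 is 80.3%. The sample size is not in question.

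**Assumed input.** Let f be the fraction of true quitters whose cotinine is at or above 20 ng/ml because of NRT. The protocol gives no NRT rate, so f is shown as a range. An observed rate is then p × (1 − f).

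**Method.** Enumerate both binomials with n = 172 per arm and sum the probability that the lower 95% limit for BSCT minus TAU exceeds −0.05.

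**Equal f in both arms:**

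| f | Observed TAU / BSCT when true rates are 10% / 5% | False non-inferiority, Wald | Newcombe | Power at true 10% v 15%, Wald | Newcombe |
|---|---|---|---|---|---|
| 0 | 10% / 5% | 3.1% | 2.4% | 81% | 80% |
| 0.1 | 9% / 4.5% | 4.7% | 3.5% | 81% | 79% |
| 0.3 | 7% / 3.5% | 10.9% | 7.8% | 81% | 79% |
| 0.5 | 5% / 2.5% | 25.4% | 18.1% | 83% | 80% |

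At f = 0.3, for example, the true difference of −5 points is observed as 3.5 − 7 = −3.5 points, which lies inside the margin. The normal approximation gives the same pattern: 2.5%, 3.8%, 9.1% and 23.1% at f = 0, 0.1, 0.3 and 0.5.

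**Unequal f:**
- f = 0.3 in TAU and 0.1 in BSCT: true 10% / 5% is observed as 7% / 4.5%. False non-inferiority is 18.8% (Wald) or 14.8% (Newcombe).
- f = 0.1 in TAU and 0.3 in BSCT: true 10% / 15% is observed as 9% / 10.5%. Power falls to 54% (Wald) or 52% (Newcombe).

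**The case against.** **The scale of the planning rates.** The Sample size section gives the 10% for TAU as a cotinine-validated rate and the 5% floor as a validated rate. If the earlier programme also validated without an NRT exception, some NRT loss is already in the 10%, and multiplying by (1 − f) counts it twice. On the validated scale, the error at 10% v 5% is simply the f = 0 row. This objection stands as a limit on the numbers. The documents do not say how that programme treated NRT. It does not remove the mechanism: abstinent NRT users are still recorded as smokers.

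**The range for f.** Advice on medication is not supply. No rate or duration of NRT use is given, and not every NRT user need reach 20 ng/ml. At f = 0.05 the error is only 3.8% (Wald) or 2.9% (Newcombe). This also stands. A reader might take the f = 0.5 row as the expected damage, or conclude that the trial cannot control its error rate. The documents support neither.

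**Power and differential use.** Power at the design rates is almost unaffected under equal misclassification. The documents give no positive reason to expect NRT use to differ by arm, since the medication advice comes in a session delivered identically. Equally, nothing rules a difference out in an open-label trial that changes the delivery of half the sessions.

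**A uniform rule is even-handed.** Cotinine for everyone applies one test, whereas CO for NRT users brings in a shorter detection window for patients who declare NRT. That is a genuine trade-off, which a cotinine-only sensitivity analysis and NRT use reported by arm would expose. It does not justify a primary rule that conflicts with the protocol's own treatment of NRT as something other than smoking.

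**Conclusion.** The point holds as a should-fix. Followed as written, the plan counts an abstinent patient with NRT-raised cotinine as a smoker and excludes the CO reading from the same visit that could correct it. This is a stated rule and not a detail left to an analysis plan.

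Its size cannot be derived from the protocol. The rise in false non-inferiority to 4.7% / 3.5% at f = 0.1 and 10.9% / 7.8% at f = 0.3 (Wald / Newcombe) is an illustration. It assumes that 10% v 5% are true smoking-abstinence rates, that the fraction f of quitters is misclassified, and that f is equal in both arms. Unequal NRT use could push the result either way.

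A reader might infer that the sample size is wrong or that the primary analysis is invalid. Neither follows: the 172 per group reproduces, and power at 10% v 15% stays at 79% to 83%.

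**What to change.** Replace the two differing CO clauses (Measurements; Exhaled carbon monoxide level) and extend the Primary outcome section with one hierarchy, applied to self-reported abstainers at each of the two checks:

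1. Not using NRT, usable saliva: validated if cotinine is below 20 ng/ml.
2. Using NRT, or saliva missing or unusable: validated if same-visit CO is below the protocol's existing 5 ppm cut-off.
3. Neither available: smoker.

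Patients who do not report abstinence, or who are lost to follow-up, remain smokers as now.

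Take NRT status from the item already scheduled at months 3 and 15, with its recall period tied to the saliva sampling date. Report NRT use by arm, and repeat the primary comparison with the cotinine-only classification as a sensitivity analysis.

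**Cost.** Endpoint wording, a date reference on an existing question, and one additional analysis. No new visit or assay is needed, and the sample size calculation is unchanged. The disadvantage is CO's shorter detection window among NRT users, which the sensitivity analysis makes visible.
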